### Technical Solution Deployment and Release

Given that the project relies on deploying the releasing of technology and devices, special attention has been paid on the planning of the releases. To be more specific, the off-the-shelf activity trackers (Wavelet Health wristbands) are delivered first (home study phase 1). The activity tracker will be set up to synchronize its raw data to the server through an app installed on the smartphones of patients. Patients not owning a smart device compatible with the provided software and hardware will be provided one. Synchronization will be done periodically through the day without any need for the patients to interact with the app installed in their phones. The app will synchronize in the background all gathered raw data, which will then be analyzed on the server to derive all meaningful features. Figure 4 presents a schematic approach of the wearable monitoring attached in the protocol.

**Figure 4 figure4:**
[figure not shown]
Wearable devices used to evaluate patient protocol adherence.

Next, the webFitForAll platform along with the MentorAge device, which embeds a depth and RGB image sensor, will be introduced to patients in lab settings in order to train them on how to interact with it. MentorAge will be installed to monitor body movements by extracting and analyzing the body’s skeleton and silhouette. MentorAge operates on Android OS and can support any graphics, thus being able to act as an end-user terminal. To do so, a mini projector will be plugged in and set up by team members in MentorAge to display the e-coaching output to any home predefined surface, taking into account unobtrusiveness and patient acceptability. After an introductory session, patients will have the exergaming platform installed at their homes (home study phases 2 and 3). Safety precautions and instructions on how to perform exercises will be given by a nurse.

## Results

Patient recruitment is completed, and the project has progressed through phase 2. In total, 10 patients have been included in the study, and baseline clinical and patient-reported outcome data are retrieved. All participants included were male with a mean age of 63.60 (SD 8.78) years suffering from HF due to coronary heart disease (8/10, 80%) or arterial hypertension (1/10, 10%) while 1 (10%) patient suffers from dilative HF. The majority of participants (7/10, 70%) reported active employment status. The most common comorbidity of participants was diabetes mellitus whereas other conditions mentioned were arterial hypertension, chronic kidney disease, and chronic obstructive pulmonary disease. In terms of their social status, 9 of 10 participants live with their family, and 80% (8/10) of participants were married. The majority of patients had preserved functional capacity, classified as NYHA class II (6/10, 60%). The mean distance walked on the 6-minute walk test was 443.00 (SD 99.78) meters. Phases 2 and 3 of the pilot study are expected to be completed within 6 months.

## Discussion

### Expected Outputs and Potential Impact

The main challenge of the BioTechCOACH-ForALL project is changing attitudes of older age HF patients toward a more active lifestyle through an e-coaching system. To achieve this scope, the project implements two studies, a lab experimental study and an at-home staggered 3-phase pilot study, the former being a preparatory step for the realization of the latter. Thorough clinical evaluation preceding each study and phase will ensure patients safety. Lab study will explore the design elements (visual appearance) of the virtual agent that make it more engaging to the patient and will allow the choice of the most suitable ones for implementation of the e-coaching intervention during home study. Home study phase 1 will provide valuable information on patient clinical capacity and daily activity levels that will be used to build an individualized exercise program to be used in home study phases 2 and 3. The third and most challenging phase (home study) of the described protocol will implement an e-coaching system to provide personalized recommendations received by the patient in the comfort of their home. Main innovation points of the envisioned e-coaching technology implementation and evaluation include (1) radical new human-computer interaction paradigms through projected content on home surfaces, (2) neuroscience-backed design of virtual agents as coaches for the patients, and (3) large-scale analytics of continuous, real-life outcome metrics passively generated by patients.

### Strengths and Limitations

An important strength of this study is the fact that is the first to examine the potential of neuroscience-backed e-coaching toward patient activation and adoption of active lifestyle by HF patients. There is currently a significant gap with respect to the adoption and use adherence by chronic patients of eHealth interventions delivered at home.

This study also has some limitations. As heart failure with reduced ejection fraction is more common in men than in women (who in turn are more susceptible to heart failure with preserved ejection fraction), the percentage of male participants is expected to outrange that of females. So far, only male participants have accepted and started the study. In addition, as the inclusion criteria indicate, only patients with adequate level of technology proficiency can participate in the study. This fact complicates the generalizability of the results for older HF patients and women in particular.

The second limitation is that the nature of this study (single-case series) does not allow for a distinct control group. Each case will serve as both control and intervention participant, and analysis will be performed on an individual basis. However, one of the main strengths of this evaluation design is its real-life nature and that any validity threats will be mitigated by detailing the context and participants when results are reported.

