### Statistical Analysis

Continuous variables with normal distribution will be reported as mean and standard deviation, while those with nonnormal distribution as median and interquartile range. Categorical variables will be expressed as frequencies and percentages. Continuously data collected will be explored for normality assumption by means of a Shapiro-Wilk test to calculate the appropriate descriptive statistics [47].

Repeated measured analysis of variance or Friedman test will be used to assess changes on continuous data with normal and nonnormal distribution, respectively, between baseline, follow-up, and end-of-study visits. Possible associations between variables will be investigated using Pearson or Spearman correlation coefficients. We estimated sample size conducting power analysis using G*Power software (version 3.1). We performed repeated measures analysis of variance (3 time conditions) using 80% power, a medium effect size of 0.25, and significance level of 5%. The sample size was estimated to be 28 participants. One-third of this patient population that will agree to proceed to home study (phases 1 through 3) will enter the next steps of study protocol [48]. All statistical analyses will be performed using SPSS Statistics version 23.0 (IBM Corp) or R for Windows version 3.1.3 (R Foundation for Statistical Computing).

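### The home study is described as analysed patient by patient, but the only tests of change named are group tests, and the two descriptions are not reconciled

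*Protocol article*

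**What the plan says.** Strengths and Limitations describes the home study as a single-case series without a separate control group, and continues: "Each case will serve as both control and intervention participant, and analysis will be performed on an individual basis". General Design fits that description: it calls the study a multiple-baseline, within-subject, single-arm design.

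Statistical Analysis describes something else. For change over time it says: "Repeated measured analysis of variance or Friedman test will be used to assess changes on continuous data with normal and nonnormal distribution, respectively", applied "between baseline, follow-up, and end-of-study visits". No individual-level method appears there.

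On normality it says: "Continuously data collected will be explored for normality assumption by means of a Shapiro-Wilk test to calculate the appropriate descriptive statistics". No other normality criterion is given.

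On numbers, "The sample size was estimated to be 28 participants", based on 3 time conditions, 80% power, effect size 0.25 and a 5% level. The home study then takes "One-third of this patient population that will agree to proceed to home study". Clinical Assessment schedules four on-site visits, and says that daily steps are measured continuously and compared across phases.

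**The concern.** A repeated-measures ANOVA or Friedman test gives one statement about the group. It cannot say whether a given patient became more active when exergames or e-coaching were introduced, which is what a single-case series analysed individually sets out to show. An analyst who follows Statistical Analysis will not produce the individual analysis promised in the limitations text. One who follows the limitations text has no method to apply.

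Two features of the named tests add to this. First, if the choice between them rests on a normality pre-test in so few patients, the hypothesis can change from outcome to outcome (means for ANOVA, within-patient ranks for Friedman) for unreliable reasons. Second, both tests in their usual form need a complete row of visits per patient, which is costly in a group this small.

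**Working it through.** **1. The two statements side by side.**

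| Place | Unit of analysis | Method named |
|---|---|---|
| Strengths and Limitations | individual patient | none |
| Statistical Analysis | group | repeated-measures ANOVA or Friedman |

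No section ranks the two or links them.

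**2. The plan's own sample size.** Within-factor repeated-measures ANOVA, one group: λ = f²·N·m/(1−ρ), df1 = m−1, df2 = (N−1)(m−1). The plan gives f = 0.25, m = 3 and α = 0.05. It does not give ρ = 0.5 or sphericity; these are assumed as software defaults.
- N = 28: λ = 0.0625 × 28 × 3 / 0.5 = 10.5, df 2 and 54, power 0.812.
- N = 27: power 0.796.

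So 28 reproduces.

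**3. Home-study size.** 28/3 = 9.3, about 9. Results reports 10 patients included, so 9 to 10 is used below.

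**4. Shapiro-Wilk at that size** (5% level, simulated rejection rates).

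| Distribution | n = 9 | n = 10 | n = 28 |
|---|---|---|---|
| lognormal, log-SD 0.6 | 28% | 32% | – |
| lognormal, log-SD 0.5 | 22% | 25% | 69% |
| exponential | 39% | 44% | 96% |
| t, 3 df | 17% | 19% | 43% |

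At 9 or 10 patients, clearly nonnormal data pass more often than not.

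**5. Complete rows.** Inputs: 9 patients, four visits (Clinical Assessment), baseline always observed, and independent missingness p at each of the three later visits. The value of p is assumed, because the document gives none. Expected complete patients = 9(1−p)³.
- p = 5%: 9 × 0.857 = 7.7
- p = 10%: 9 × 0.729 = 6.6
- p = 20%: 9 × 0.512 = 4.6

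With only the three time points named in Statistical Analysis, p = 10% leaves 9 × 0.81 = 7.3.

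**6. Power with four conditions** (f = 0.25, assumed ρ = 0.5).
- n = 9: λ = 0.0625 × 9 × 4 / 0.5 = 4.5, df 3 and 24, power 0.345.
- n = 7: λ = 3.5, df 3 and 18, power 0.26.

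The level depends heavily on ρ. At n = 9, ρ = 0.3 gives λ = 3.21 and power 0.25; ρ = 0.8 gives λ = 11.25 and power 0.74.

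**7. What using all visits gains.** On complete data under compound symmetry, a random-intercept model matches repeated-measures ANOVA. With 9 patients, p = 10% per post-baseline visit and ρ = 0.5, simulation puts the complete-case variance of the baseline-to-end contrast at about 1.3 times that of an analysis using all observed visits.

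**The case against.** The sentence in the limitations section explains why there is no control group, so analysis on an individual basis could mean only that each patient is their own control. Both named tests are within-subject tests and would fit that meaning. Group and individual analyses can also be run side by side. A reader might therefore infer that the two statements are incompatible, but the document does not support that: they are unreconciled. The own-control reading does not remove the problem, because the single-case-series and multiple-baseline labels favour an individual analysis and no method for one is named.

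Four further inferences are tempting and go beyond the text.
- That the plan selects the test by Shapiro-Wilk. The sentence ties that check to descriptive statistics. Its role in choosing the test is a natural inference, since tests are assigned by normality and no other criterion appears, but it is not stated.
- That the plan drops patients with a missed visit. It says nothing on this. Deletion is how the named tests usually run, and a missing-data rule may properly sit in an analysis plan that is not shown. Its absence is not a finding.
- That daily steps are reduced to one value per phase. This is not stated, and Wearable Monitoring plans within-day and between-day series.
- That the group tests cause the low power. It comes mainly from having about 9 patients, and a mixed model will not cure that.

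The figure of 9 is itself uncertain. The Abstract gives 28 for both studies, and Patient Population says that all included patients do the home phases. At 28 the pre-test and missing-visit points weaken considerably; the mismatch in the unit of analysis remains at any size.

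**Conclusion.** The concern holds as a failure to reconcile. The limitations text promises an individual analysis, the statistical section offers only group tests, and those tests cannot deliver the promise. This rests on the text alone and needs no assumption.

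The quantitative support is conditional. It assumes 9 to 10 home-study patients, that Shapiro-Wilk is what decides between the tests, and a missed-visit rate between 5% and 20%. On those terms the pre-test misses a clearly skewed lognormal (log-SD 0.6) roughly 70% of the time, and between about 1.3 and 4.4 of 9 patients drop out of a complete-row analysis (9 − 7.7 and 9 − 4.6). Going from 9 to 7 complete patients lowers four-condition power from 0.345 to 0.26 at ρ = 0.5. The documents do not show that the trial's conclusion would differ between the two routes. The change is worth making because it is cheap and settles what will be reported.

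**What to change.** **Visit outcomes.** Name one main analysis: a linear mixed model with a random patient intercept and visit as a factor, using all available visits, with a small-sample degrees-of-freedom correction. Do not choose the test by a normality pre-test. Keep Friedman or a permutation test as a sensitivity analysis.

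**Daily steps.** Fit a mixed model to daily or weekly values, with phase as a factor and within-patient serial correlation. Report the group phase effect and each patient's own phase change.

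**Limitations text.** Have it refer to the steps model, so that the individual analysis has a stated method.

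**Cost.** Revised analysis wording and somewhat more modelling; no new data or visits. With so few patients the correlation structure must be kept simple. Check that the software version used offers the chosen small-sample correction, which the documents do not show.

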## Appendix

Multimedia Appendix 1 Peer-reviewer report from the funding agency.

## Abbreviations

EEG: electroencephalogram
HF: heart failure
NYHA: New York Heart Association
